## **12. Concomitant therapy**

Not applicable

## **13. Security laboratory**

Not applicable

## **14. Stopping criteria**

### **Individual**

The approval of the study participants (patients, family caregivers and pharmacy staff) can be withdrawn at any time without indicating reasons and without any disadvantages.

### **Total study**

The study will be discontinued if, contrary to the expectations, a potential risk should exist for the study participants.

## **15. Statistical method**

### **Statistical design**

The error rate of the intervention group will be compared to the error rate of the control group by the chi-square test. The error rate of the medication administration before patient education will be compared to the error rate after the training by the McNemar test. A  $p\text{-value} \leq 0.05$  is considered as statistically significant. Feasibility of the education method into the daily routine of the community pharmacy and the contentment of the patients and family caregivers will be analyzed qualitatively. The influence of co-variables like dosage form, patient characteristics, educating person and number of drugs on the education success will be determined by logistic regression.

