#### **4. Aims and issues of the project**

##### **Primary outcome**

- Rate of incorrect medication administration will be compared between control and intervention group at 6-month follow-up.

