## **6. Study design**

Prospective, cluster-randomized, controlled interventional study.

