**Calculation of sample size based on the primary outcome**

Due to the results of a randomized study which has compared a complex education intervention for the correct application of inhalers with a standard consultation, we presume a difference for the success of the intervention in the control- and intervention groups of 20%, with success rates of  $p_1=32\%$  and  $p_2=52\%$  [22]. To determine a significant difference between the control- and intervention group by the chi-square test (unrelated sample,  $\alpha = 0.05$ ;  $\beta = 0.8$ ), it is required, in due consideration of a drop-out rate of 15% after 6 months, a cluster size of 5 community pharmacies per group and a cluster effect (Intraclass Correlation Coefficient, ICC) of 0.02,  $n=122$  medication administrations of a dosage form e.g. eye drops or transdermal patches per group. With a cluster size of 10 community pharmacies per group the sample size of the dosage form increases to  $n=133$  per group. The calculation of the sample size is carried out on the level of dosage forms because then patients who apply for various dosage forms can be educated according to their individual drugs. The follow-up visit after 12 months will be described qualitatively.

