**16. Ethical and legal aspects**

The study is conducted according to the current version of the Declaration of Helsinki of the World Medical Association and the ethical principles for research on humans.

The study protocol will be submitted to the responsible ethics committee of the medical faculty Heidelberg for evaluation before the beginning of the study. It will not be started with the inclusion of study participants unless the written affirmative vote of this ethics committee is available.

Until the inclusion of the patients or their family members for the follow-up, the study serves to ensure quality assurance of the consultation quality of the pharmacy staff in the participating community pharmacies. The demonstration of the application by the medication user and the following consultation by the pharmacist can already take place during routine counseling. The pharmacy staff will document the work load within this quality-assuring project, for example additional time effort or interruption of work routine for evaluating the feasibility for daily use of the training. If patients or their family caregivers do not agree to participate in the study, the data on medication administration that was collected during the consultation might be used for

[figure not shown]

evaluation of the consulting quality. Pseudonymization does not happen because there is no follow-up for these patients or their family caregivers.

The participation of all participants in this study is voluntary.

The pharmacy staff of the participating community pharmacies will be informed in written and oral form before the beginning of the study about the nature and scope of the planned intervention, in particular about the possible benefits and risks or burdens, the voluntariness of the participation and about the required documentation of their approval by signing the declaration of consent. To cluster the educated medication users not only according to the community pharmacy but also according to the educating person, the pharmacy staff will get a pseudonym which indicates their profession (e.g. pharmacist or pharmacy technician) and their professional experience (less than a year, 1-5 years, more than 5 years).

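### The protocol randomises pharmacies but names an ordinary chi-square test for the primary comparison; at its own ICC the true two-sided error rate is about 6% to 10%, depending on how its cluster size is read, not 5%.

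*Protocol*

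**What the plan says.** Protocol section 6 describes the design as "Prospective, cluster-randomized, controlled interventional study", and section 11 confirms that each pharmacy is wholly control or wholly intervention. The primary outcome in section 4 is: "Rate of incorrect medication administration will be compared between control and intervention group at 6-month follow-up".

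Section 15, Statistical design, names the between-group test: "The error rate of the intervention group will be compared to the error rate of the control group by the chi-square test". Significance is judged at a p-value of 0.05 or less. The sample size paragraph repeats the choice: "To determine a significant difference between the control- and intervention group by the chi-square test (unrelated sample". Clustering enters that paragraph only as an allowance in n, through "a cluster size of 5 community pharmacies per group and a cluster effect (Intraclass Correlation Coefficient, ICC) of 0.02".

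The logistic regression in section 15 is for predictors of training success. It lists the educating person among its covariates, but no pharmacy term and no random effect. Section 16 explains why staff receive pseudonyms: "To cluster the educated medication users not only according to the community pharmacy but also according to the educating person". It names no test that would use that grouping.

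**The concern.** The protocol accepts that outcomes within a pharmacy are correlated when it sets n, then names a test that assumes they are not. Enlarging the sample protects power; it does not correct the size of the test. The chi-square statistic divides the observed difference by a standard error that omits between-pharmacy variation, so its p-values are too small on average when the intervention has no effect. A primary result with p just under 0.05 could not be taken at its stated level.

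This is not a detail that a protocol may leave to a statistical analysis plan. A specific test is named in two places, and a later plan with a cluster-adjusted test would contradict the protocol.

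**Working it through.** **Inputs (Protocol section 15).** Success rates 32% and 52%; alpha 0.05; power 80% (printed as beta = 0.8); dropout 15%; ICC 0.02; n = 122 per group with 5 as the stated cluster size and n = 133 with 10. Sidedness is not stated, but only a two-sided 0.05 reproduces n. Equal allocation and equal pharmacy sizes are assumed.

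**Step 1: reproduce the stated n.** Pooled two-proportion formula without continuity correction, mean rate 0.42:

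n = [1.96 × √(2 × 0.42 × 0.58) + 0.8416 × √(0.32 × 0.68 + 0.52 × 0.48)]² / 0.20² = 94.4, so 95 per group.

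Design effect DE = 1 + (m − 1) × 0.02, then division by 0.85:

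- m = 5: 95 × 1.08 = 102.6, so 103; 103 / 0.85 = 121.2, so **122**.
- m = 10: 95 × 1.18 = 112.1, so 113; 113 / 0.85 = 132.9, so **133**.

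Both figures reproduce exactly, but with 5 and 10 used as administrations per pharmacy. The text calls them pharmacies per group. Both readings are therefore carried forward.

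**Step 2: true size of the unadjusted test.** With no intervention effect, the chi-square z-statistic has variance of about DE instead of 1, so the true two-sided size is 2 × [1 − Φ(1.96 / √DE)]. Analysed numbers are 122 × 0.85 = 103.7 and 133 × 0.85 = 113.05 per group.

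| Reading | Administrations per pharmacy (m) | DE | 1.96/√DE | True size |
|---|---|---|---|---|
| 5 pharmacies per group | 103.7 / 5 = 20.74 | 1.395 | 1.660 | 9.7% |
| 10 pharmacies per group | 113.05 / 10 = 11.3 | 1.206 | 1.785 | 7.4% |
| 5 administrations per pharmacy | 5 | 1.08 | 1.886 | 5.9% |
| 10 administrations per pharmacy | 10 | 1.18 | 1.804 | 7.1% |

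**Step 3: simulation check.** Beta-binomial data, ICC 0.02, common true rate from 0.32 to 0.52, 200,000 runs per setting:

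- 5 pharmacies × 21 administrations per group: 9.2% to 9.9%.
- 10 × 11: 7.1% to 7.5%.
- 21 × 5: 5.4% to 5.9%.
- 12 × 10: 6.5% to 7.2%.

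A t-test on pharmacy-level proportions stayed between 4.9% and 5.1% in all four layouts.

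**Step 4: power of the valid test at the planned numbers.** SE = √[DE × (0.2176 + 0.2496) / n]; non-centrality = 0.20 / SE; non-central t with 2k − 2 degrees of freedom, where k is the number of pharmacies per group.

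- k = 5, n = 104: DE 1.396, SE 0.0792, non-centrality 2.53, 8 df: power 60%.
- k = 10, n = 113: DE 1.206, SE 0.0706, non-centrality 2.83, 18 df: power 76%. Simulation at 10 × 11 gives 75%.
- Other reading, 21 pharmacies × 5: DE 1.08, SE 0.0693, non-centrality 2.89, 40 df: power 80%.
- Other reading, 11 pharmacies × 10: DE 1.18, SE 0.0708, non-centrality 2.83, 20 df: power 77%.

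**The case against.** **Clustering is not overlooked.** The sample size carries an ICC, and section 16 says that users will be grouped by pharmacy and educator. One could argue that a cluster-adjusted chi-square test is implied. The text does not support this: both mentions of the test are unqualified, and the second specifies unrelated samples. What stands is that the grouping is intended and pharmacy membership is known, so the repair is easy.

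**The inflation may be small.** On the reading that reproduces 122, the error is 5.9%. A Yates correction would also lower the simulated figures under the literal reading, to about 7.3% to 8.4% with 5 pharmacies and 5.3% to 6.6% with 10. The first point is fair and is the reason for giving a range. The second does not rescue the plan: the protocol mentions no such correction, its n does not use one, and the error still exceeds 5% in those layouts.

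**Stronger readings that the document does not support.**

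- A reader might infer that section 15 ignores the educator as well. It does not; the educating person is a named covariate of the logistic regression. Only pharmacy is missing.
- A reader might take 7% to 10% as the firm range. That holds only if 5 and 10 are pharmacies per group.
- A reader might quote much larger error rates by assuming a higher ICC. The protocol gives 0.02 and no basis for more.
- A reader might add that confidence intervals will be too narrow. Section 15 specifies p-values only.

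**Conclusion.** The point holds. The named primary test does not match the randomisation, and its nominal 5% level is exceeded on either reading: 9.7% or 7.4% with 5 or 10 pharmacies per group, and 5.9% or 7.1% with 5 or 10 administrations per pharmacy. The direction is known and anti-conservative, and it affects the primary outcome, so the test should be replaced before any data are analysed.

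These figures rest on the protocol's ICC of 0.02, a two-sided test without continuity correction, equal pharmacy sizes, 15% dropout and one dosage form analysed at a time. If dosage forms were pooled, with several administrations from one participant, the added correlation would tend to raise the error further; that has not been quantified here.

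**What to change.** In section 15, replace the chi-square test with a cluster-valid primary analysis. Two suitable choices are:

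- a t-test on pharmacy-level 6-month error proportions with 2k − 2 degrees of freedom, k being the number of pharmacies per group; or
- a mixed-effects logistic regression with a random pharmacy intercept and a small-sample correction.

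With so few pharmacies the t-test is the simpler choice. Add pharmacy as a random effect to the covariate regression, keeping the educating person as a covariate, and report the observed ICC. State plainly whether 5 and 10 are pharmacies per group or administrations per pharmacy.

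**Cost.** No new data are needed, but this is more than a change of wording. With 5 or 10 pharmacies per group, the t-test has about 60% or 75% power at 32% versus 52%, so the 80% claim must be restated for the valid analysis and the number of pharmacies or n revisited. As a guide for 5 pharmacies per group, solving n = 95 × [1 + (n/5 − 1) × 0.02] gives n = 95 × 0.98 / (1 − 95 × 0.02 / 5) = 150.2 analysed. Dividing by 0.85 gives 177 enrolled per group, against the stated 122. That uses a normal approximation; a t-test with 8 degrees of freedom would need more. If the intended design has about 21 pharmacies per group with 5 administrations each, the loss of power is negligible.

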With methods respecting the individual level of the patients or family caregivers, progress to change their behavior may be positively influenced [20]. Thus, studies for improving the compliance show that considering the individual levels influences the outcome of the intervention positively [21]. The model has not been applied yet for trainings to avoid medication errors. Yet it seems to be obvious that patients or family caregivers, who do not realize a medication error because they have not been aware of it, do not recognize the necessity for training. To reach these patients and family caregivers and to motivate them for training, the Transtheoretical Model could be the theoretical framework for implementing training interventions.

According to this prospective randomized controlled study, standardized patient education in community pharmacies should be evaluated. The training method should consider the patients’ or family caregivers’ lack of awareness if necessary and particularly should be integrated in the daily routine of pharmacies. For this reason, the pharmacy staff of the particular community pharmacy will carry out the training and document any additional work required. Before the study is started, the pharmacy staff will be informed about incorrect and correct administration of the dosage form which is known from literature (see inclusion criteria), the use of education materials and the study procedure. There are three follow-up visits planned, approximately one month, six months and twelve months after the first patient education. Patients or family caregivers will either be addressed in the community pharmacy (recruiting and follow-up visits) or they will be contacted by employees of the participating community pharmacies or by an employee of the department of Clinical Pharmacology and Pharmacoepidemiology and they will

be invited into the correspondent community pharmacy (follow-up visits). The pharmacy staff or employees of the department of Clinical Pharmacology and Pharmacoepidemiology will again assess the quality of medication administration of patients or family caregivers during their follow-up visits to evaluate the sustainability of the first training.

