##### **Secondary outcomes**

- Rate of incorrect medication administration before and after patient education in the control and intervention group.
- Rate of incorrect medication administration during the course of follow-up visits.
- Influence of the consideration of the individual level according to the Transtheoretical Model [20] on the willingness to participate in a training, i.e. long-term (1, 6 and 12 months) correct drug use.
- Univariate and multivariate analyses to evaluate the influence of covariates such as dosage form, patient characteristics, the training person and the number of medicines on training success.
- Qualitative: feasibility of implementation in community pharmacies, satisfaction of patients and caregivers.

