##### **The following general questions are related to the project:**

- Is it possible to motivate patients or family caregivers to attend training by raising awareness of a drug administration error?
- Is the consideration of the individual awareness of the error an advantage in the training compared to a "normal" counseling?
- Is the training success sustainable?
- Is the patient education intervention feasible in the community pharmacy setting?
- Are any differences in training success depending on the dosage form or person?

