## **11. Study procedure**

The study will be carried out in community pharmacies with which other projects have already established cooperation. Prior to the start of the study, pharmacy staff will be informed of erroneous and correct administration of the different dosage forms (see inclusion criteria) known from the literature, the use of study materials, and the study procedure. After written informed consent of the head of the pharmacy and pharmacy staff, the pharmacies will be assigned to control or intervention group (cluster randomization). There will be exclusive control pharmacies and intervention pharmacies.

Pharmacy staff addresses potential study participants according to the inclusion criteria during daily routine in the community pharmacy. It is possible within the scope of this study to train the use of different dosage forms for the same patient or family caregiver. In order to identify a potential administration error, the pharmacy staff asks the patient or family caregiver to use the medicine (duration approx. 2-5 minutes). Such a demonstration is quite common in the context of the usual pharmaceutical counseling. The demonstration can be performed with the patient's drug itself or with a placebo. The pharmacy staff assesses a possibly incorrect administration by using a checklist defined in advance for a specific dosage form. Checklists and placebo materials are provided by the Department of Clinical Pharmacology and Pharmacoepidemiology. In the control group, pharmacy staff provides a standard consultation (duration approx. 3 minutes) followed by the provision of standardized information material, e.g. written step-by-step

instructions. In the intervention group, the staging algorithm (Fig. 1) is used to determine the individual level of the patient or caregiver according to the Transtheoretical Model. The stage "Maintenance", i.e. the permanent correct use of the drug, cannot be detected with this algorithm. The purpose of this model is to identify in particular those medicines users who are not aware of administration errors despite incorrect use of the drug and who may not be motivated to seek training or detailed counseling.

[figure not shown]

Figure 2. Staging Algorithm

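### The secondary regression on the educating person has no pharmacy or educator term, although Section 16 announces clustering by both, so p-values for staff characteristics will tend to be too small

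*Protocol*

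**What the plan says.** Section 15 (Statistical design) gives the model: "The influence of co-variables like dosage form, patient characteristics, educating person and number of drugs on the education success will be determined by logistic regression". It does not say whether the educating person means the individual or that individual's characteristics. It does not list arm among the covariates, and it names no term for pharmacy or educator.

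Section 4 makes this a secondary outcome: "Univariate and multivariate analyses to evaluate the influence of covariates such as dosage form, patient characteristics, the training person". One of the project's general questions in the same section reads "Are any differences in training success depending on the dosage form or person".

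Section 16 treats the educator differently. Its stated purpose is "To cluster the educated medication users not only according to the community pharmacy but also according to the educating person", and for this "the pharmacy staff will get a pseudonym which indicates their profession (e.g. pharmacist or pharmacy technician) and their professional experience", the latter in three bands.

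Two further statements fix the structure. Section 3 says "the pharmacy staff of the particular community pharmacy will carry out the training and document any additional work required". Section 11 says "There will be exclusive control pharmacies and intervention pharmacies". Together they nest each educator in one pharmacy and one arm. This is an inference about practice; the protocol does not state it as a rule.

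**The concern.** Profession and experience are properties of the educator, so every user trained by the same person has the same value. The information about such a covariate comes mainly from the number of educators and pharmacies, not from the number of administrations. A logistic regression that treats administrations as independent overstates that information and gives standard errors that are too small.

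The protocol recognises the dependence twice, through the ICC in its sample-size paragraph and through the clustering purpose in Section 16. The regression sentence carries neither forward. An analyst who follows Section 15 literally could report that pharmacists and technicians differ in training success, or that experience matters, more often than the 5% level allows when nothing is there.

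**Working it through.** **Inputs from the protocol.** Success rates 32% and 52%, ICC 0.02, 122 administrations per group with 5 pharmacies per group, "a drop-out rate of 15% after 6 months", significance at 0.05 (two-sided assumed).

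**Inputs assumed.** 2 or 3 educators per pharmacy, and an extra educator-level ICC (ρe) of 0 to 0.10. The protocol gives neither. ICCs are on the latent logistic scale.

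**The protocol's own figure.** There is none for this regression; the sample size only supplies n. With pooled variance, n = [1.96·√(2·0.42·0.58) + 0.8416·√(0.32·0.68 + 0.52·0.48)]² / 0.20² = (1.368 + 0.575)² / 0.04 = 94.4, so 95 per group. Then 95 × (1 + 4 × 0.02) / 0.85 = 120.7, close to the stated 122. This arithmetic takes the 5 as administrations per pharmacy, whereas the text calls it pharmacies per group. That is a separate matter and does not bear on this point. After dropout, 0.85 × 122 = 103.7, about 104 analysed per arm for one dosage form.

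**Approximation by hand.** With m administrations per educator, the variance for an educator-level covariate is understated by about DEFF = 1 + (m − 1)(0.02 + ρe). A nominal 5% test then rejects with probability 2Φ(−1.96/√DEFF). For 5 pharmacies per arm, m = 104/10 = 10.4 with 2 educators each and 104/15 = 6.93 with 3. Example: 1 + 9.4 × 0.02 = 1.188, and 1.96/√1.188 = 1.80, which gives 7.2%.

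**Check by simulation.** 6,000 trials per setting, arm and profession in a plain logistic model, no true profession effect:

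| Educators per pharmacy | ρe | DEFF | Approximation | Simulated |
|---|---|---|---|---|
| 2 | 0 | 1.188 | 7.2% | 6.3% |
| 2 | 0.02 | 1.376 | 9.5% | 8.4% |
| 2 | 0.05 | 1.658 | 12.8% | 10.5% |
| 2 | 0.10 | 2.128 | 17.9% | 14.4% |
| 3 | 0 | 1.119 | 6.4% | 5.5% |
| 3 | 0.02 | 1.237 | 7.8% | 6.7% |
| 3 | 0.05 | 1.415 | 9.9% | 8.8% |
| 3 | 0.10 | 1.712 | 13.4% | 11.7% |

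The approximation runs slightly high because ICCs on the latent scale are smaller on the observed scale. Other simulations of the same design gave 6.5-8.0% at ρe = 0, and up to 16% at ρe = 0.10. Overall: about 7% with no extra educator ICC, and about 7-16% with one of 0.02-0.10.

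**Sensitivity.**
- Zero ICC at both levels: 4-6%, so the excess comes from the clustering.
- One educator per pharmacy, 5 pharmacies per arm: 10% at ρe = 0 and 17% at ρe = 0.05 for profession; 10% and 26% for experience.
- 10 pharmacies per arm, 133 per group, 2-3 educators: 5-6% at ρe = 0 and 8-9% at ρe = 0.05 for profession.
- Three dosage forms pooled, each reaching its n (309 per arm), 5 pharmacies per arm: about 8-10% at ρe = 0, rising to about 24-32% at ρe = 0.10, because each educator then contributes more administrations.

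**Identity or characteristics.** With 5 pharmacies per arm and 3 educators each, intercept, arm and 29 educator indicators make 31 columns of rank 30, because the arm column is the sum of the indicators of that arm's educators. The arm effect is then not estimable. Profession and experience vary within arms. With random staffing they could be fitted alongside arm in 92-94% of simulated trials with one educator per pharmacy and 5 pharmacies per arm, and in practically all others. The standard error of the arm effect rises by 4-30%.

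**The case against.** The best defence is that logistic regression does not exclude random intercepts, that Section 16 states the clustering intent, and that coding and degrees of freedom belong in an SAP, which is not at hand. Part of this stands: the two sections are compatible in principle, and small-sample details need not be in the protocol. But Section 15 is where the analysis is fixed, and it lists the educating person beside ordinary covariates with no link to the clustering. An SAP that follows it literally would inherit the fault.

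A reader might infer more than the documents support:

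- **Educator and arm cannot be separated.** True only for educator identity as fixed effects. The protocol does not say identity is used, and the pseudonym in Section 16 points towards profession and experience.
- **Educator effects will be falsely significant because they are confounded with arm.** For profession and experience the excess comes from ignored clustering, not aliasing. At the stated ICC it is modest and a risk, not a certainty.
- **The model will often fail because some educators have only correct or only incorrect users.** This again presumes identity. High rates arise only with one dosage form's n, whereas the regression has dosage form as a covariate and so pools forms. With 3 educators per pharmacy the rate falls to about 5-20% with three forms and 0.4-4% with five.
- **Department staff who re-train go uncoded.** Section 11 lets department staff evaluate follow-up demonstrations but does not say who re-trains.

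The word person in the general question may also mean the user; the secondary outcome is the clear basis for this point.

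**Conclusion.** The point holds in a limited form. The regression in Section 15 omits the clustering that Section 16 announces, and p-values for staff-level covariates would be too small if it were followed as written. The size is modest at the protocol's own ICC (about 7% instead of 5%) and reaches about 7-16% only with an assumed educator ICC of 0.02-0.10. Pooling several dosage forms makes it larger; more pharmacies make it smaller. These figures rest on assumed educator numbers and educator ICCs. Separately, Section 15 leaves open what the educating person means, and the identity reading as fixed effects would remove the arm effect from the model. Only a secondary, exploratory analysis is affected; the primary comparison at 6 months is not.

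**What to change.** Amend the regression sentence in Section 15 to say that:

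- the educating person enters as profession and experience band, together with arm;
- the model accounts for clustering by pharmacy and by educator within pharmacy, either with random intercepts or with cluster-robust inference and a small-sample correction. Either serves.

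The cost is about one sentence. The pharmacy assignment and the staff pseudonym are already planned, so no new data are needed. The downside is that p-values for staff-level covariates become less favourable, which reflects how few educators and pharmacies stand behind them.
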